### Data analysis

The quantitative data analysis will be performed using Statistical Package for Social Sciences (SPSS) version 21 based on Intention-to-treat analysis. The cluster design will be taken into consideration during analysis and cluster effect will be reported. Descriptive statistical analysis will include calculation of sample means, standard deviation (SD) and proportions according to the type of variables. Categorical variables will be compared using chi-square test. Within group changes in quantitative variables from baseline to endline at six months will be analysed using a paired *t*-test. Unpaired *t*-tests will be applied to independent samples for between group comparisons. In order to explore potential differences between groups (e.g. socio-economic, age groups and gender etc.) multivariable regression analysis will also be used.

The FFQ data will be entered into the spreadsheet software used in the PURE study [34]. This software determines the amount of food (from the food list) consumed by the individual, by multiplying the average consumption with frequency of intake and portion size of the food item. The intake of each food item will then be re-computed for a day, and then multiplied with the nutrient amount per gram to obtain the daily nutrient intake from each food. The estimated nutrient intakes per day will then be summed to obtain the total daily nutrient intakes.

Participants’ nutrient intakes per day will be compared against the NIN dietary guidelines to calculate the percentage of participants meeting the guidelines for fat, sugar, salt, fruit and vegetable intake. Sub-group analysis by disease status will also be performed. Changes in fat, sugar, salt, fruit and vegetable intake in both the groups will be calculated as post-intervention minus pre-intervention nutrient intakes. The net intervention effect will be calculated as the change in dietary intake in the intervention arm minus the change in dietary intake in the control arm from baseline to the study end at six months (difference in differences method) [37]. Dietary information collected through food purchase and consumption records will also be used to calculate the change in per capita monthly consumption of fat, sugar, salt and fruit and vegetables for each family. The clinical significance of changes achieved will be estimated based on association of nutrient intakes with clinical outcomes reported in existing literature.

BMI will be calculated as weight (Kg) divided by height (m)^2^. Blood samples for haemoglobin, fasting plasma glucose and lipid profile, and urine samples will be analysed using standard laboratory methods. The 24 h urinary sodium excretion (mg/day) will be estimated from a single morning fasting urine sample using the Kawasaki formula [38].

Participants will be classified into five stages of change separately for fat, sugar, salt, fruit and vegetable intake: Pre-contemplation, Contemplation, Preparation, Action and Maintenance stage on the basis of quantitative data. Stage will also be assessed based on qualitative data in relation to people’s knowledge of dietary intake guidelines and their perception and awareness about their own dietary intakes and dietary practices.

The use of specific components of the intervention, satisfaction with the program and ideas for improvement will be analyzed by summarising the answers to open ended questions from the feedback proforma. Website use will be measured through feedback regarding login by number of participants and the visitor count.

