### Sampling

A multi-level sampling strategy will be used. Twelve clusters, based on the type of housing (LIG, MIG and HIG), have been selected bearing in mind that there is sufficient geographic separation to avoid any spill-over effect of the intervention. Similar clusters will be paired together to form six pairs. For each of the six pairs, computer generated randomisation will be used to allocate clusters to intervention and control groups by a researcher not involved in the study. The number of clusters and cluster size will be fixed. Equal numbers of families will be recruited from each cluster through systematic random sampling. One adult (35–70 years) per family will be randomly selected as the index case for the baseline and post-intervention assessment.

One family champion (the adult member who cooks food most of the time) will be selected from each family for the implementation of the intervention. In recognition of the fact that not all family champions will be using information technology tools or mobile phones (as demonstrated through the formative research), one co-champion will also be selected from each family. A co-champion can be any person from the family identified by the family champion who would be able to assist him/her in using the internet and mobile phone communications.

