### Sample size

Sample size calculations were done for each of the outcome variables: fat, salt, and fruit and vegetable intake, but not for sugar intake, because estimates of sugar intake were not available. The prevalence of adequate dietary intake for the different foods and nutrients was used to calculate the sample size for fat and fruit and vegetables based on dietary surveys and based on urinary salt excretion for salt. As no similar trials were available to inform an assumption of improvements in the intervention arm, the sample size was calculated based on a 20% improvement. Sample size for estimation of change in salt required the largest sample size. Based on a previous study, which indicated that 15% of adults had a salt intake of <5 gram per day [25], and assuming a 20% improvement in the intervention arm, power calculations (alpha = 0.80; p = 0.05) indicated that 83 participants would be needed per study arm. As the intra-cluster correlation co-efficient was not available for the outcome of interest, we used a design effect of 2, which increased the estimated sample size to 166 [26]. Taking into account a drop-out rate of 10%, we calculated that 183 participants would be required [27]. However, in order to enable comparison of outcomes between different age and socio-economic groups, the calculated sample size had to be doubled. Thus, a final sample size of 366 participants per study arm was deemed to be sufficient to assess changes in each of the study outcome.

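### The analysis promises to account for clustering, but the only between-arm tests it names are individual-level tests in their ordinary form, and the six randomised pairs are not mentioned

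*Protocol article*

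**What the plan says.** On design, the Sampling section of the protocol article states "Twelve clusters, based on the type of housing (LIG, MIG and HIG), have been selected" and "Similar clusters will be paired together to form six pairs", with one cluster of each pair allocated to each arm. "Equal numbers of families will be recruited from each cluster through systematic random sampling", and one index adult per family is measured. The Sample size section says that no ICC was available, uses a design effect of 2, and ends with "a final sample size of 366 participants per study arm was deemed to be sufficient".

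On analysis, the Data analysis section first gives a general commitment: "The cluster design will be taken into consideration during analysis and cluster effect will be reported". It then names its tests. "Categorical variables will be compared using chi-square test". A paired t-test is for change within each arm. Unpaired t-tests "will be applied to independent samples for between group comparisons". Multivariable regression is mentioned only for exploring differences by factors such as socio-economic group, age and gender. The net effect is defined as a difference in differences, without a standard error or test. The section names no clustered method and does not refer to the pairs.

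**The concern.** The commitment and the named tests point in different directions. An analyst who applies the tests in their usual form gets an analysis that treats everyone in a cluster as independent, which the plan's own design effect of 2 contradicts. An analyst who keeps the commitment has to modify or set aside the tests, and the document does not say how.

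The primary outcome is the percentage of participants meeting each dietary guideline. That is a categorical variable, and chi-square is the only test named that fits it. Unadjusted, p-values would be too small and confidence intervals too narrow for all five dietary components, so an ineffective intervention could too easily be declared effective.

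**Working it through.** **Inputs from the document.** 12 clusters in six pairs, equal numbers per cluster, one adult per family, 366 per arm, design effect 2, drop-out 10%.

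**The plan's own figure.** Two proportions, 15% against 35%, two-sided 5%, 80% power, continuity correction: 83 per arm, as stated. Then 83 × 2 = 166; 166 × 1.10 = 183; 183 × 2 = 366; and 366 / 6 = 61 per cluster. The stated chain reproduces if the 20% improvement is read as percentage points.

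**Type I error of an unadjusted test.** If the true variance of the arm difference is DE times what the test assumes, the two-sided error at nominal 5% is

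2 × (1 − Φ(1.96 / √DE)), with DE = 1 + (m − 1) × ICC.

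- DE = 2, the plan's value: 1.96 / √2 = 1.386, so the error is 16.6%. At m = 61 this implies ICC = 1/60 = 0.017.
- With about 55 completers per cluster (366 × 0.9 / 6) and the same ICC, DE = 1.9 and the error is 15.5%.
- If the design effect of 2 was meant for the undoubled 183 / 6 = 30.5 per cluster, then ICC = 1 / 29.5 = 0.034. At 61 per cluster DE = 1 + 60 × 0.034 = 3.0, and the error is about 26%. This reading is an assumption.
- Other assumed ICCs at m = 61: 0.005 gives 8.6%, 0.01 gives 12.1%, 0.05 gives 32.7%.

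**Effect of matching.** If pairs explain a share s of the between-cluster variance, that share cancels in the arm difference and the ratio becomes 1 + (m − 1) × ICC − m × ICC × s. With ICC = 1/60 and s = 0.5, this is 2 − 61/60 × 0.5 = 1.49, and the error is 10.9%.

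**Check by simulation.** A continuous outcome, six pairs, 61 per cluster, no intervention effect, 40,000 trials per setting:

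| Share of between-cluster variance explained by pairs | Unadjusted t-test, DE 2 | Unadjusted t-test, DE 3 |
|---|---|---|
| 0% | 16.5% | 25.8% |
| 25% | 13.8% | 21.5% |
| 50% | 10.9% | 16.7% |
| 75% | 8.0% | 11.1% |
| 100% | 4.9% | 4.7% |

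In the same trials, a paired t-test on the six pair differences (5 df) gave 4.7% to 5.1% in every setting. An unpaired t-test on the 12 cluster means (10 df) gave about 5% with no pair effect and 0.5% to 3.7% when pairs explained 25% to 100%. Separate runs with 6 against 6 clusters of 55 and ICC 0.018 gave 16.5% for an ordinary chi-square test, so the inflation is much the same for a binary outcome.

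**The case against.** The strongest reply is that the document does commit to considering the cluster design, and does so before it names any test. A chi-square statistic can be adjusted for clustering (Donner–Klar, Rao–Scott), and an unpaired t-test can be run on cluster means, where it holds its level. The choice of adjustment may sit in a fuller protocol or analysis plan that is not shown.

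Much of this stands. A reader might infer that the plan ignores clustering, or that the named tests cannot be made to respect it; the documents support neither. The link between the chi-square sentence and the primary outcome is also an inference, because that sentence directly follows the one on descriptive statistics.

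It does not dispose of the point. The article is not silent in a way that leaves the method open: it names specific between-arm tests, describes the t-test as one for independent samples, and gives no unit of analysis or adjustment that would reconcile them with the commitment.

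A reader might also infer that leaving out the pairs adds to the false-positive risk. It does not. Effective matching lowers the error of an unadjusted test, and ignoring pairs in a cluster-level test makes that test conservative. Clusters were matched for similarity within housing type, a socio-economic proxy, so some benefit is plausible. The reason to use the pairs is that the analysis should follow the randomisation and not waste power.

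**Conclusion.** The point holds as an unresolved conflict: a general promise to account for clustering, followed by between-arm tests that in their ordinary form do not, and no use of the six randomised pairs.

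The size is conditional. About 17% in place of 5% follows from the plan's own design effect of 2, provided that the tests are run unadjusted and matching brings no benefit. If pairs explain half of the between-cluster variance the figure is about 11%; if they explain all of it, the error is nominal. About 26% needs the further assumption that the design effect referred to the cluster size before doubling, so a flat range of 17% to 26% should not be read as the trial's false-positive risk. The ICC is unknown, and none is given for change scores, on which the difference in differences rests.

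**What to change.** In the Data analysis section, replace the between-arm chi-square and unpaired t-tests with one named primary method:

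- (a) an analysis of the six within-pair differences in cluster-level summaries (mean change in intake, or percentage meeting the guideline), using t with 5 df; or
- (b) a mixed model, linear for intake and logistic for meeting the guideline, with a random cluster effect, pair or housing type as a fixed effect, and a small-sample degrees-of-freedom correction.

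Under either option, report the ICC from a model with a cluster effect, which also delivers the promised report of the cluster effect. Apply the chosen method to the difference-in-differences estimate so that it has a standard error.

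The cost is a change of wording and intervals wider than the unadjusted tests would give. No new data are needed.

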## Abstract

Nutrition is an important determinant of health. At present, nutrition programs in India mainly emphasize improving maternal and child nutrition. Adult nutrition has not received due attention, though diseases like hypertension and diabetes are largely preventable through changes in dietary and physical activity behaviour. Little is known about the best approaches to improve dietary behaviours, especially the role of modern information technology (IT) in health education. We describe the protocol of the SMART Eating (Small, Measurable and Achievable dietary changes by Reducing fat, sugar and salt consumption and Trying different fruits and vegetables) health promotion intervention. A Cluster Randomised Controlled Trial will evaluate the effect of an IT-enabled intervention on nutrition behaviour among urban adults of Chandigarh, India. Formative research using a qualitative exploratory approach was undertaken to inform the intervention. The IT-enabled intervention programme includes website development, Short Message Service (SMS), e-mail reminders and interactive help by mobile and landline phones. The IT-enabled intervention will be compared to the traditional nutrition education program of distributing pamphlets in the control group. The primary outcome will be the percentage of study participants meeting the dietary intake guidelines of the National Institute of Nutrition, Hyderabad, India and the change in intake of fat, sugar, salt, fruit and vegetables after the intervention. The difference in differences method will be used to determine the net change in dietary intakes resulting from the interventions. Measurements will be made at baseline and at 6 months post-intervention, using a food frequency questionnaire. The formative research led to the development of a comprehensive intervention, focusing on five dietary components and using multi-channel communication approach including the use of IT to target urban North Indians from diverse socio-economic backgrounds. The Cluster Randomised Controlled Trial design is suitable for evaluating the effectiveness of this IT-enabled intervention for dietary behaviour change.

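### The arm effect on dietary intakes is fixed as a difference of raw changes; adjusting for the baseline intake already collected would be valid too and somewhat more precise

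*Protocol article*

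**What the plan says.** The Data analysis section of the protocol article first defines change in each intake: it "will be calculated as post-intervention minus pre-intervention nutrient intakes". It then defines the arm effect, with the control arm as comparator: "The net intervention effect will be calculated as the change in dietary intake in the intervention arm minus the change in dietary intake". The Abstract confirms that this is the intended analysis: "The difference in differences method will be used to determine the net change in dietary intakes resulting from the interventions".

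The baseline value is available for every component, since "Measurements will be made at baseline and at 6 months post-intervention, using a food frequency questionnaire".

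The other methods in Data analysis are general. For quantitative outcomes, "Unpaired *t*-tests will be applied to independent samples for between group comparisons". For proportions, "Categorical variables will be compared using chi-square test". Regression is given an exploratory role: "In order to explore potential differences between groups (e.g. socio-economic, age groups and gender etc.) multivariable regression analysis will also be used". On clustering: "The cluster design will be taken into consideration during analysis and cluster effect will be reported". None of these sentences names baseline intake, or baseline guideline status, as a covariate.

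The Primary outcome section defines the primary outcome as the change in the percentage of participants meeting the national guidelines. The Abstract also counts the change in intakes as primary.

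**The concern.** In a randomised comparison, a change score carries the measurement noise of both questionnaires. It also assumes that a baseline difference between arms would persist in full to the end of the study. With a correlation below 1, part of a chance difference fades by itself, so subtracting all of it goes too far. If the intervention arm happens to start with the higher fat intake, the estimated reduction is flattered; if it starts lower, the reduction is understated.

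Twelve clusters are randomised, so some baseline difference between arms is to be expected. Pairing on housing type balances socio-economic status, but not intake directly. What is at stake is precision, and how far one realised result depends on the luck of the allocation. The validity of the trial is not in question.

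**Working it through.** **Inputs from the protocol article.** Sampling: 12 clusters in six pairs, with equal numbers of families per cluster. Sample size: design effect 2 and 366 participants per arm.

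**The plan's own figure.** Comparing 15% with 35% (20% read as percentage points), two-sided 5% level, 80% power, with continuity correction, gives 83 per arm. Then 83 × 2 = 166, 166 × 1.10 = 182.6, rounded to 183, and 183 × 2 = 366. The figure reproduces. It uses no baseline–endline correlation, so nothing in it depends on the present point. Cluster size is 366 / 6 = 61, and a design effect of 2 implies an intra-cluster correlation of 1 / (61 − 1) = 0.0167.

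**Assumption.** The correlation r between baseline and six-month intake is not in the document, so a range is shown.

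**Step 1: individual-level precision.** Relative to the variance of the endline value alone (set to 1), the variance is 2(1 − r) for a change score and 1 − r² after linear adjustment. The ratio of adjusted to change score is (1 − r²) / [2(1 − r)] = (1 + r) / 2. The standard error (SE) of the change score relative to the adjusted one is √[2 / (1 + r)].

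| Assumed r | Change score | Adjusted | Variance ratio | Relative SE of change score |
|---|---|---|---|---|
| 0.3 | 1.40 | 0.91 | 0.65 | 1.24 |
| 0.5 | 1.00 | 0.75 | 0.75 | 1.15 |
| 0.7 | 0.60 | 0.51 | 0.85 | 1.08 |
| 0.8 | 0.40 | 0.36 | 0.90 | 1.05 |

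**Step 2: chance imbalance.** With design effect 2 and 366 per arm, the baseline difference between arms has a standard deviation of √(2 × 2 / 366) = 0.105 outcome SD. Given a baseline difference d, the change-score estimate moves by (r − 1)d. For d = 0.105 that is −0.073, −0.052 and −0.031 SD at r = 0.3, 0.5 and 0.7. The sign is opposite to that of the imbalance, which is the over-correction.

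**Step 3: the clustered design.** A simulation of 4,000 trials per row, with 12 clusters of 61, intra-cluster correlation 1/60 and no pairing, compared the change score with adjustment for the participant's own baseline. Because cluster means may be more stable over time than individual values, r was set separately at the two levels. Imbalance here is the baseline difference between arms.

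| r, individual | r, cluster | SE, change | SE, adjusted | SE reduction | Correlation with imbalance: change | Correlation with imbalance: adjusted |
|---|---|---|---|---|---|---|
| 0.3 | 0.3 | 0.125 | 0.099 | 21% | −0.61 | −0.03 |
| 0.3 | 0.8 | 0.100 | 0.091 | 8% | −0.48 | 0.28 |
| 0.5 | 0.5 | 0.105 | 0.092 | 12% | −0.48 | 0.01 |
| 0.5 | 0.8 | 0.088 | 0.081 | 8% | −0.42 | 0.19 |
| 0.7 | 0.7 | 0.083 | 0.076 | 8% | −0.40 | −0.02 |
| 0.7 | 0.9 | 0.067 | 0.065 | 3% | −0.29 | 0.18 |

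Adjustment was the more precise in every row, by about 3% to 21% in SE. Where the two correlations are equal, the adjusted estimate is almost unrelated to the imbalance. Where cluster means are the more stable, some dependence remains, though less than for the change score.

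**The case against.** Difference in differences is a recognised estimator. It subtracts the baseline difference, is unbiased over randomisations, and matches objectives that the plan words as reductions and increases. All of this stands. A reader might infer that the plan leaves baseline imbalance in the intake results or biases them. The documents do not support that: the effect in step 2 is conditional on the imbalance that happens to occur, and averages to zero over allocations.

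The size is uncertain. No r is given, the figures in step 1 ignore clustering, and the simulation omits the pairing, which may itself reduce imbalance. This stands, and it is why a range is shown.

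A covariate may also cost more than it earns with so few clusters. In a paired analysis of cluster means, 5 degrees of freedom become 4, and the critical t rises from 2.571 to 2.776 (2.776 / 2.571 = 1.08). That 8% would cancel the gain at r = 0.7. The objection is right for a covariate fitted to cluster means, but a participant-level covariate spends no cluster-level degree of freedom.

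Two general claims for adjustment would go too far here. It does not remove all dependence on imbalance, as step 3 shows. Nor does the large-sample guarantee of precision carry over to a logistic odds ratio, where adjustment generally enlarges the standard error of the log odds ratio and changes the estimand.

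Finally, a reader might infer that the primary percentage will be tested by a chi-square on endline status alone, or has no between-arm analysis of change. The chi-square sentence is general. It is not tied to the guideline percentages or to the endline, and the exact model may stand in a fuller document. That reading remains an inference.

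**Conclusion.** The point holds for dietary intakes as a matter of efficiency. The article writes out a change-score estimator in two places and does not use the baseline intake as a covariate, so this is a choice it fixes and not a detail left open. The choice is valid but less precise than it could be. The individual-level standard error is about 24%, 15% or 8% larger than with adjustment if r is 0.3, 0.5 or 0.7. In the 12-cluster design the gain from adjusting may be as small as about 3%, if r is 0.7 for individuals and 0.9 for cluster means. The estimate also moves against any chance baseline imbalance. These sizes rest on assumed correlations, the stated design effect of 2, 61 participants per cluster and no modelling of the pairs.

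For the percentage meeting guidelines, the documents support only a recommendation, because the planned method for that comparison is not stated specifically enough to be called wrong.

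**What to change.** Estimate the arm effect on each intake from a linear model of the six-month value. Include arm, the participant's own baseline intake of the same component as an individual-level covariate, the pair, and a term for cluster, with a small-sample correction suited to 12 clusters. Keep the difference-in-differences table as a descriptive display.

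For the percentage meeting each guideline, a parallel cluster- and pair-aware model with baseline guideline status as covariate is advisable. Report the result as a marginal risk difference, so that the non-collapsibility of the odds ratio does not change what is being estimated.

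The cost is one covariate per model and a sentence or two in the analysis section. No new data and no additional participants are needed, and no cluster-level degree of freedom is spent. The change should be recorded before the endline data are examined.

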### Primary outcome

The primary outcome for the study is the % change in study participants meeting India’s National Institute of Nutrition (NIN) dietary guidelines for fat, sugar, salt, fruit and vegetable intake. The NIN recommend that, for adults, 20–30% energy should be from fat (10% from visible fat and 10–20% from foods other than visible fat); no more than 20 g sugar for women and 25 g sugar for men, less than 5 g salt, and at least 100 g of fruits and 300 g of vegetables per day.

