### Secondary outcomes

Secondary outcomes include % change in body weight, and mean change in body mass index (Kg/m^2^), blood pressure (mm Hg), haemoglobin (g/dL), fasting plasma glucose (mg/dL), total serum cholesterol (mg/dL), high-density lipoprotein (mg/dL), low-density lipoprotein (mg/dL), triglycerides (mg/dL) and urinary salt excretion (g/day).

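### The effect on dietary intake is fixed as an unadjusted difference in differences; adjusting the six-month value for baseline would be more precise at almost no cost

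*Protocol article*

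**What the plan says.** The Data analysis section defines change in each intake as a simple subtraction, which "will be calculated as post-intervention minus pre-intervention nutrient intakes", and then takes the difference between arms, with control as the comparator: "The net intervention effect will be calculated as the change in dietary intake in the intervention arm minus the change in dietary intake". The Abstract repeats the choice: "The difference in differences method will be used to determine the net change in dietary intakes resulting from the interventions". It also counts change in intake as part of the primary outcome.

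The between-arm tests named are "Unpaired *t*-tests will be applied to independent samples for between group comparisons" and "Categorical variables will be compared using chi-square test". The section says that clustering will be taken into account, without naming a model. Regression appears once, for another purpose: "In order to explore potential differences between groups (e.g. socio-economic, age groups and gender etc.) multivariable regression analysis will also be used". Baseline intake is not named as a covariate.

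The Primary outcome section is on a binary scale: "The primary outcome for the study is the % change in study participants meeting India’s National Institute of Nutrition (NIN) dietary guidelines". The secondary measures are worded as changes too: "Secondary outcomes include % change in body weight, and mean change in body mass index", followed by blood pressure, blood tests and urinary salt.

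**The concern.** Clusters are randomised and, according to the Sampling section, one index adult per family is assessed both before and after the intervention. Each dietary outcome therefore comes with its own baseline value. Difference in differences subtracts that value in full, which is the best use of it only when baseline and endline correlate perfectly. Below that, full subtraction carries baseline noise into the estimate. Given a chance baseline gap between arms, it also overcorrects that gap by the fraction 1 − r.

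Intakes come from a self-reported food frequency questionnaire, so a correlation near 1 is not to be expected. With six clusters per arm, chance baseline gaps are plausible. What is at stake is the width of the confidence intervals for the intake effects, above all in the comparisons with least information. Because the article states this estimator outright, the choice is not a detail left to an analysis plan.

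**Working it through.** **1. The plan's own sample size.** The Sample size section gives 15% with adequate salt intake, a 20% improvement and 83 per arm. Reading the improvement as 20 percentage points (15% vs 35%), with two-sided 5% and 80% power:
- n = [1.96·√(2·0.25·0.75) + 0.8416·√(0.1275 + 0.2275)]² / 0.20² = 72.4
- with continuity correction: 72.4/4 · [1 + √(1 + 4/(72.4·0.20))]² = 82.1, so 83, as stated
- chain: 83 × 2 = 166; 166 × 1.10 = 183; 183 × 2 = 366 per arm

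This is a comparison of two proportions at one time point. No correlation or standard deviation of change enters it. The single-time-point basis is inferred from the match; the section does not state it.

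**2. Variance of the estimators.** Set the variance of an unadjusted endline comparison to 1, with equal variances at both times:
- difference in differences: 2(1 − r)
- baseline-adjusted endline: 1 − r²
- ratio of the two: 2(1 − r)/(1 − r²) = 2/(1 + r), above 1 for every r below 1

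Difference in differences is also less precise than ignoring baseline altogether when 2(1 − r) > 1, that is, when r < 0.5.

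**3. Size on cluster means.** Twelve clusters give six per arm, so m = 366/6 = 61. The correlation of cluster means is

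r = [ICC·CAC + (1 − ICC)·IAC/m] / [ICC + (1 − ICC)/m],

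with ICC the intra-cluster correlation, CAC the cluster autocorrelation and IAC the individual baseline-to-endline correlation. All three are assumptions. The lower ICC is what a design effect of 2 implies at m = 61: 1/60 = 0.017.

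| ICC | CAC | IAC | r | 2/(1+r) |
|---|---|---|---|---|
| 0.017 | 0.5 | 0.3 | 0.40 | 1.43 |
| 0.017 | 0.7 | 0.5 | 0.60 | 1.25 |
| 0.05 | 0.7 | 0.5 | 0.65 | 1.21 |
| 0.05 | 0.9 | 0.7 | 0.85 | 1.08 |

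The excess variance runs from about 8% to 43%.

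**4. Overall power at the actual size.** On the protocol's own figures, 366 × 0.9 / 2 = 164.7 effective participants per arm. Suppose the planning case were analysed as a difference in differences of proportions, with variance 2(0.1275)(1 − r) + 0.1275 + 0.2275 − 2r√(0.1275·0.2275) and a normal approximation:
- r = 0: variance 0.610, power 91%
- r = 0.1: variance 0.550, power 93%
- r = 0.3: variance 0.431, power 97%

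**5. Where the loss falls.** The doubling was made for age and socio-economic comparisons, so a half-sample subgroup has about 83 effective per arm. The same formula there gives 69% at r = 0.1, 79% at r = 0.3, 85% at r = 0.4 and 90% at r = 0.5, against 86% for endline only. Break-even is near r = 0.43.

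**6. Degrees of freedom.** A purely cluster-level model with intercept, arm and five pair terms leaves 12 − 7 = 5 degrees of freedom; adding baseline leaves 4. The squared ratio of t quantiles is (2.776/2.571)² = 1.17. This cancels the gain when 2/(1 + r) < 1.17, that is, when cluster-mean r exceeds about 0.71.

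**The case against.** Difference in differences is a recognised method and is unbiased here, so nothing invalid is planned. That stands, and it limits the point to efficiency.

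A reader might infer that the stated 80% power is not delivered. The documents do not support that. Powers of 69% to 79% arise only at 83 per arm, before the design effect and the doubling. At the recruited size the overall comparison stays above 80% even at r = 0. The calculation also applies difference in differences to guideline attainment, for which the plan names a chi-square test.

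A reader might likewise say that the estimator contradicts the sample size. The two concern different outcomes: the difference-in-differences sentence is about continuous intake, the sample size about a threshold. The single-endline basis is itself only inferred.

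It is also too strong to say that every interval is wider than it need be. With 12 clusters, a cluster-level analysis that spends a degree of freedom on baseline can lose what it gains when r is high. Converting the unclustered ratio into a number of participants lost would ignore the clustering and overstate the loss. These limits stand. They are the reason to adjust at individual level, and they do not remove the gain available there.

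**Conclusion.** The point holds as a matter of precision. The article fixes an unadjusted change-score contrast for the intake effects and assigns no baseline-adjusted model to them. The variance ratio 2/(1 + r) follows from algebra; its size does not, because the article gives no r. Over the assumed ranges the excess on cluster means is about 8% to 43%.

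There is no bias. There is also no demonstrated shortfall in overall power, on the protocol's 10% dropout and design effect of 2 and a normal approximation that makes no allowance for the small number of clusters. The cost falls mainly on the age and socio-economic comparisons. Against an unadjusted endline comparison a loss arises only at low correlation: below 0.5 for continuous intakes and below about 0.43 in the binary planning case. The change is worth making because it is nearly free, not because the present plan would mislead.

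**What to change.** - For each continuous intake, define the main effect as the between-arm difference at six months from an individual-level model that accounts for clustering. Include arm, matched pair and the participant's baseline value of the same variable, and use small-sample degrees of freedom.
- For guideline attainment, adjust for baseline intake or baseline status in the same way and report a percentage-point difference.
- Keep difference in differences as a sensitivity analysis.
- The same adjustment can be used for weight, body mass index, blood pressure, blood tests and urinary salt without redefining those outcomes. Expect little gain where the baseline-to-endline correlation is high.

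The cost is analysis wording and one extra covariate per model; no new data are needed. If the analysis is done purely on cluster means, the fall from 5 to 4 degrees of freedom can cancel the benefit when the cluster-mean correlation is high, so the individual-level model should be the one specified.
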